# Immunonutrition Supplement for Reducing Acute Oral Mucositis in Head and Neck Cancer Radiotherapy

## Literature Review

Head and neck cancer is the sixth most common cancer worldwide that accounts for more than 550,000 cases and 300,000 deaths annually. In Thailand, the incidence rate was about 110,000 per year in 2011 which was the third and the fifth most common cancer in men and women, respectively.

Radiotherapy plays an important role of head and neck cancer treatment. It is used as a single modality of treatment in early stage, and combination with chemotherapy in locally advanced stage. Post-operative radiotherapy with or without chemotherapy is also performed in head and neck cancer patient underwent surgery with adverse pathologic features.

Even though the effectiveness of radiotherapy and chemotherapy for head and neck cancer treatment, the side effects of each modality of treatment can cause the deteriorated effect of the patient. Both treatments also trigger pro-inflammation process.

Acute side effects of radiotherapy are including oral mucositis, esophagitis, dermatitis, decrease taste, thickening of saliva, etc. which initiate from the inflammation process of irradiated tissue. Mucositis of oral cavity, pharynx, and esophagus is resulted in the severe pain and swallowing difficulty caused the poor nutrition intake and weight loss.

Immunonutrition (IN) is the supplement that contains elements including specific amino acids such as arginine and glutamine,  $\omega$ -3 fatty acids, and nucleotides which are able to modulate the immunity. Arginine and glutamine are conditionally essential amino acids especially in stress conditions. Arginine is essential element for production of nitric oxide, polyamines, proline, creatinine, and glutamate. It can increase number of T helper cell. Glutamine can protect integrity of gastrointestinal mucosa, promote immunity by being the nutrient for rapidly dividing cells such as immune cells, and is the precursor of arginine.  $\omega$ -3 fatty acids such as fish oil can limit the conversion of linoleic acid into arachidonic acid and replace  $\omega$ -6 fatty acids in cell membrane, therefore, it can reduce the inflammation process. Nucleotides, although have less well-defined role, are believed that they can help T cell functions.

Supplementation of IN shows the promising outcome in cancer care. In surgical series, perioperative IN showed improvement of treatment outcomes. In head and neck cancer, and gastrointestinal cancer surgery, IN support reduced systemic inflammatory response syndrome, post-operative complication rate, and length of stay. Based on the evidences, the European Society for Clinical Nutrition and Metabolism (ESPEN) guideline for cancer treatment recommends perioperative and postoperative IN support for cancer surgery and as a part of enhanced recovery after surgery (ERAS) protocol in colorectal surgery.

In many radiotherapy series, IN reduced hematologic toxicity, reduced inflammation, and improved immunity based on various measurement methods of inflammatory and immunity. Machon et al. demonstrated that IN before concurrent chemoradiotherapy (CCRT) significantly reduced C-reactive protein (CRP) and  $\alpha$ -1 acid glycoprotein, but IN

during CCRT did not show statistical difference of CRP and  $\alpha$ -1 acid glycoprotein between at the beginning of CCRT comparing with at the end of CCRT. Zheng et al. did the meta-analysis and found that IN reduced the severe toxicities (oral mucositis, diarrhea, esophagitis), and maintained weight after the treatment compared to standard nutrition support.

Addressing the effect of IN on head and neck cancer, Chitapanarux et al. investigated a study comparing IN containing arginine, glutamine, and omega-3 fatty acid that provided daily during CCRT and no intervention in 40 head and neck cancer patients treating with CCRT. The result showed that serum albumin at the end of CCRT was higher, no significant weight loss, more completion of treatment, and less grade 3-4 hematologic toxicity in IN arm. However, there were no significant difference in the weight during the treatment and the rate oral mucositis between two groups. Assenat et al. performed a phase II study evaluating effect of IN enriched with L-arginine, omega-3 fatty acid, and ribonucleotide in 40 head and neck cancer underwent CCRT. IN was prescribed 1 week before each of tri-weekly chemotherapy during CCRT. The findings indicated that there was a non-significant less mucositis in patients who complied with IN more than 75% compared to less than 75% ( $p=0.082$ ). Boisselier et al. performed a randomized control trial comparing IN which contained the same ingredient and prescribed as Assenat et al.'s study and isocaloric isonitrogenous nutrition in 180 patients. The data indicated that IN support in postoperative chemoradiotherapy in head and neck cancer didn't reduce acute oral mucositis, still, it improved long term survival. Lyra et al. performed a systematic review and metaanalysis and found that glutamine played a significant role on reducing severity and prolonged the onset of mucositis. The combined supplements of IN had the difference results as IN contained arginine, glutamine and omega-3 showed improved oral mucositis and treatment completion, while IN that contained arginine, omega-3 and nucleotides did not show the any significant reduction of oral mucositis.

The result of the our previous trial on various types of cancer including head-and-neck cancer, esophageal cancer, and cervical cancer showed a significant lower incidence of hematologic toxicity in the IN supplement group, while non-hematologic toxicities and two-year overall survival were not difference. This was difference from the result from Boisselier et al. that showed improvement of overall survival in the group with IN that had >75% compliance. We also in-house evaluated the effect of IN on the inflammation and immunity enhancement evaluated by neutrophil-to-lymphocyte ratio (NLR) and absolute lymphocyte count (ALC) using second study's data, the IN add-on failed to demonstrate a better NLR and ALC compared to control arm, however, ALC was higher at the end of radiotherapy in head and neck cancer subgroup. The result also showed the correlation of initial ALC and NLR at pre-treatment and the values during and the end of radiotherapy.

There is no recommendation on the quantities of each ingredient in combined supplement IN should be added to the regular diet and how frequent should IN be taken during the radiotherapy. Our previous studies that provided diary IN contained protein 31.3 g (arginine 6.16 g, L-glutamine 3.07 g), and fish oil 2.73 g showed that IN reduced hematologic toxicities, but no overall survival improvement. The study result of Boisselier et al. that showed a survival benefit, they provided IN that prescribed 1 week before tri-weekly chemotherapy and contained nutrition per day including protein 50.4 g (arginine 11.4 g), eicosapentaenoic acid/docosahexaenoic acid 3.9 g, ribonucleic acids 1.35 g.

With the results of our previous studies that showed the relation of pre-treatment, during and the end of treatment ALC and NLR, and the study from Boisselier et al., we will study the effect of IN in head and neck cancer patients which will expand its use before radiotherapy to

modulate the immunity and inflammation before treatment and provide more intense of IN per day to reduce oral mucositis severity.

## Research Hypothesis

Incidence of acute oral mucositis in head and neck cancer patients who receive IN during radiotherapy will be less compared to patients who do not receive IN.

## Objective

### Primary objective

1. To determine if IN can reduce cumulative acute oral mucositis of radiotherapy.

### Secondary objective

1. To determine whether immunonutrition can reduce inflammation and increase immunity during radiotherapy.
2. To compare other acute side effects during radiotherapy between two arms.
3. To evaluate nutrition status during radiotherapy.

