#### Side effect evaluation

Radiotherapy acute side effect will be evaluated by CTCEA version 5 in weekly basis during radiotherapy in the following items.

- Oral mucositis
- Radiation dermatitis
- Esophagitis
- Laryngeal mucositis
- Pharyngeal mucositis
- Hematologic
  - Anemia
  - Decreased White blood cell
  - Decreased Neutrophil count
  - Decreased Lymphocyte count
  - Decreased Platelet count

Patients will also evaluate the oral mucositis and radiation dermatitis toxicities by themselves using Thai version of NCI- PRO-CTCAE.

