#### Blood test

Complete blood count (CBC), BUN and creatinine (Cr) will be evaluated at 1-2 week before, and weekly during radiotherapy. Serum albumin will be collected at 1-2 week before and first, third and seventh week of radiotherapy.

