#### Secondary Outcomes

1. Difference of the proportion of remaining grade 2-4 CTCEA toxicities of each site/system of between 2 arms.
2. Difference of the proportion of remaining cumulative grade 2-4 PRO-CTCEA toxicities of oral mucositis and radiation dermatitis of between 2 arms.

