### Statistical Analysis

The data will be presented in descriptive basis. The continuous data will be reported by using mean (or median) with standard deviation (or interquartile range). The dichotomous data will be reported using percentage or proportion. Comparing between arms will use student t-test or Wilcoxon Signed Rank Test with a significant level.

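### Two of the three secondary objectives have no matching outcome beyond graded cytopenias, and the stated between-arm tests use no baseline value, one of them being a paired test

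*Protocol*

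**What the plan says.** The *Secondary objective* section of the Protocol has three items. The first is "To determine whether immunonutrition can reduce inflammation and increase immunity during radiotherapy". The second is a between-arm comparison of other acute side effects. The third is "To evaluate nutrition status during radiotherapy".

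The *Secondary Outcomes* section has two items: "Difference of the proportion of remaining grade 2-4 CTCEA toxicities of each site/system of between 2 arms" and "Difference of the proportion of remaining cumulative grade 2-4 PRO-CTCEA toxicities of oral mucositis and radiation dermatitis of between 2 arms".

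The data for the first and third objectives are scheduled. Under *Blood test*, "Complete blood count (CBC), BUN and creatinine (Cr) will be evaluated at 1-2 week before, and weekly during radiotherapy"; serum albumin is taken before radiotherapy (RT) and at three points during it. Weight is measured weekly, and the schedule table under *Nutritional status* also places it at the pre-RT visit. Under *Side effect evaluation*, the haematological items graded weekly include "Decreased Lymphocyte count".

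The *Literature Review* reports from the group's earlier data "the correlation of initial ALC and NLR at pre-treatment and the values during and the end of radiotherapy". Its closing paragraph gives this as one reason for starting immunonutrition (IN) before RT.

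On method, *Statistical Analysis* says: "Comparing between arms will use student t-test or Wilcoxon Signed Rank Test with a significant level". It mentions no baseline term and no covariate.

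**The concern.** The objectives and the outcome list do not match. Both listed outcomes serve the second objective. For inflammation and nutrition no variable is named, and immunity is reached only through toxicity grades. The week of IN before RT rests on the idea that immunity and inflammation can be shifted before treatment, yet no listed outcome measures ALC or NLR. With no variable or time point named in advance, the choice of what to report stays open in an open-label trial.

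The stated method fits these objectives poorly. A signed-rank test compares paired values and does not suit two independent arms. The t-test is valid, but it discards the pre-treatment value that the Protocol itself describes as related to the later one. What is at stake is the precision and credibility of the mechanistic and nutritional results.

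**Working it through.** **1. Objectives against outcomes**

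| Secondary objective | Listed outcome | Data scheduled |
|---|---|---|
| Inflammation | None | CBC (allows NLR) |
| Immunity | Only graded cytopenias, through the first outcome | CBC (allows ALC and NLR) |
| Other acute side effects | Both outcomes | Weekly CTCAE; patient-rated items |
| Nutrition status | None | Albumin, weight, BMI |

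Every listed outcome is a proportion, while the named tests are designed for continuous or ranked data. So the Protocol names tests for continuous measures without naming a continuous outcome.

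**2. The plan's own sample size**

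Inputs from *Sample size*: 61% against 30.5%, power 0.8, and 0.05 (written there as beta, but it reproduces only as two-sided alpha).

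n = [1.960 × √(2 × 0.4575 × 0.5425) + 0.842 × √(0.61 × 0.39 + 0.305 × 0.695)]² / 0.305² = 40.7, so 41 per arm. With 15% dropout, 41 / 0.85 = 48.2, so 49, which the Protocol rounds to 50. The figure reproduces. It concerns the primary endpoint only; no size is given for the secondary objectives.

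**3. Cost of leaving out the baseline**

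Let r be the within-arm correlation between the baseline and the end-of-RT value. The Protocol reports a correlation without a coefficient, so r = 0.3, 0.5 and 0.7 is an assumed range. With one baseline covariate the residual variance is (1 − r²) times the unadjusted variance. The equivalent sample-size factor is 1 / (1 − r²).

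The smallest difference detectable with 80% power at two-sided 0.05, in SD units, is (1.960 + 0.842) × √(2/n) × √(1 − r²). At n = 41 unadjusted this is 2.802 × 0.221 = 0.62. Power is shown for an illustrative difference of 0.5 SD.

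| | Unadjusted | r = 0.3 | r = 0.5 | r = 0.7 |
|---|---|---|---|---|
| Residual variance | 1.00 | 0.91 | 0.75 | 0.51 |
| Sample-size factor | 1.00 | 1.10 | 1.33 | 1.96 |
| Detectable difference, 41 per arm | 0.62 | 0.59 | 0.54 | 0.44 |
| Power for 0.5 SD, 41 per arm | 62% | 66% | 74% | 89% |
| Power for 0.5 SD, 50 per arm | 71% | 75% | 82% | 94% |

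A t-test on change from baseline would not repair this. Its variance factor is 2(1 − r), that is 1.40, 1.00 and 0.60, which is larger than the ANCOVA factor at each r.

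**4. Is there a clean baseline?**

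Under *Nutrition support*, IN starts 1 week before RT. The baseline blood test falls 1-2 weeks before RT. A sample late in that window could follow the first intake, and adjusting for it could then remove part of the effect under study.

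**The case against.** The strongest reply is that covariates and models belong in a statistical analysis plan, which is not at hand. That would hold if the Protocol were silent. But it lists its secondary outcomes and states its between-arm tests, and both can be judged as written. It remains true that the details of a model could sit in the analysis plan, which is why the mismatch of objectives and outcomes comes first.

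Other parts of the reply stand and limit the point:

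- A reader might infer that immunity has no outcome at all. It has one: grade 2-4 low lymphocyte count falls under the first listed outcome. It is a dichotomised toxicity and measures neither NLR nor inflammation.
- A reader might infer that the nutrition objective cannot be answered. Its wording is descriptive, and the planned summaries would allow a description of weight and albumin. What is missing is a named variable and time point.
- A reader might infer that the unadjusted t-test is biased or invalid. Allocation is randomised 1:1, so it is unbiased and keeps its error rate. The cost is precision.
- A reader might infer about seven tests per marker, one for each week. The Protocol schedules weekly samples but does not say that each week will be tested.
- A reader might take the factor of 1.96 as the expected loss. It needs r = 0.7, which nothing in the Protocol establishes. At r = 0.3 the gain is small.

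**Conclusion.** The point holds in this limited form. The outcome list does not cover inflammation, ALC or NLR as levels, or nutrition, although two secondary objectives call for them and the measurements are scheduled. The signed-rank test does not fit a comparison of independent arms. The t-test is sound but gives up precision that the trial already collects, worth a factor between 1.10 and 1.96 over the assumed range of r.

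These figures assume a linear relation, the same r in both arms, about 41 evaluable patients per arm for the laboratory values, and a baseline taken before IN. They ignore any gain from adjusting for centre. Only the secondary objectives are concerned.

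**What to change.** 1. In *Secondary Outcomes*, add the difference between arms in ALC, log NLR, albumin and weight at the end of RT.
2. In *Statistical Analysis*, compare each of these by ANCOVA with the baseline value and centre (the stratification factor) as covariates, reporting the adjusted difference with a 95% confidence interval.
3. Replace the signed-rank test by the Wilcoxon rank-sum test for any unadjusted non-parametric comparison between arms.
4. State that the baseline CBC and albumin within the 1-2 week window are drawn before the first IN intake, and weigh the patient at the same visit.
5. Define the end of RT. The last albumin is scheduled in week 7, and courses with a lower total dose (60 or 66 Gy against 70 Gy) may end sooner. The middle albumin also needs reconciling: the text gives the third week, while the table as extracted shows week 4.

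The cost is wording, a rule on when the baseline sample is drawn, possibly a moved last albumin sample for shorter courses, and a little more analysis. No new type of measurement and no additional patients are needed.

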## Population

Locally advanced head neck cancer patient treating with definitive or postoperative concurrent chemoradiotherapy in:

- Division of Radiation Oncology, Faculty of Medicine, Chiang Mai University.
- Radiotherapy section, Udonthani Cancer Hospital
- Radiotherapy section, Lampang Cancer Hospital

## Study Design

Prospective, open-label, randomized control trial

## Eligibility

### Inclusion criteria

1. Age range between 18 – 70-year-old
2. Histologically confirmed squamous cell carcinoma of head and neck.
3. Locally advanced head and neck cancer planning to treat with concurrent chemoradiotherapy for definitive or postoperative setting.
4. No previous radiotherapy in head and neck area.
5. Good performance status with ECOG 0-1.
6. Laboratory tests are in the normal ranges.
7. The participant or legal representative provides the written informed consent for the study.

### Exclusion criteria

1. Histological subtypes other than squamous cell carcinoma (e.g., Adenocarcinoma, small cell carcinoma).
2. Has metastatic disease or locoregional recurrence.
3. Receive immune-enhancing nutrition product prior to the randomization within 30 days.
4. Allergy to immune-enhancing nutrition ingredients used in the study.

5. Active autoimmune disease(s) that require medication within 2 years.
6. Diabetes Mellitus, renal disease, liver disease and/or other disease that limits some nutrition or calorie intake.
7. Known disease or condition that would interfere with the cooperation of the study.
8. Pregnancy or breastfeeding.

## Material and Method

### Recruitment and Informed Consent process

Potential volunteer who is met the inclusion criteria and not in exclusion criteria will be fully explained about the study by the investigator. The volunteer will have the sufficient time to read informed consent and have the opportunity to ask any question that may have. He/she also can ask the relative or someone he/she trusts about sign the informed consent form and is informed that the process is voluntary and can be withdrawn anytime. After fully understanding and accepting to join the study, he/she will sign the informed consent form that is approved by the local ethical committee.

### Intervention Assignment

Patients will be randomized in to 2 arms:

1. IN arm
2. Control arm

### Randomization

Randomization process will be done at the screening process using central randomization with computer-generated code with block randomization and stratified by radiotherapy centers. Intervention arm will be assigned randomly in 1:1 ratio.

[figure not shown]

### Blinding

No blinding in this study.

### Nutrition support

Participant who is randomized into IN arm will receive IN 1 week before radiotherapy and daily during radiotherapy and ones in control arm will not get IN supplement. The remaining IN package will be counted in every visit.

The IN package will be provided by Thai Otsuka Pharmaceutical Co., Ltd and prepared in sachet form. Each sachet will contain 60 g powder comprising arginine 3.13 g, L-glutamine 1.56 g, and fish oil 1.39 g. It will be taken 3 sachets per day by diluted in 250 mL of water. As a result, patients who are randomized into IN arm will get 762.48 additional calories which contains 46.93 g of protein (4.68 of glutamine and 9.39 of arginine), 94.77 g of carbohydrate, and 21.74 g of fat (4.17 of fish oil).

Both arms will receive nutrition consultation every visit to ensure adequate energy intake with proper portions of macronutrients altogether with side effects of the treatment(s) and IN. Participants who experience the symptoms that limit intake such as nausea, vomiting, dysphagia, or odynophagia will be evaluated by the treating physician and receive appropriate standard treatment according to the symptom(s). Participants in IN arm are encouraged to take IN as much as they can if they have side effect(s) that limit IN intake. If patients experience a severe side effect that compromise the safety, including grade III-IV toxicity caused by IN, the IN will be withdrawn and the study will be discontinued in that particular participants.

### Radiotherapy

Patient will be treated with radiotherapy in 3D conformal or IMRT/VMAT/Tomotherapy technique. Dose of radiotherapy to primary tumor, negative margin tumor bed, and close or positive margin tumor bed are 70, 60, and 66 Gy, respectively. Dose and area of neck node irradiation depend on physician judgement.

### Chemotherapy

Platinum-based chemotherapy (cisplatin 40 mg/m^2 or carboplatin AUC 2) will be given in weekly basis during radiotherapy.

Induction chemotherapy or adjuvant chemotherapy is allowed. The induction/adjuvant chemotherapy regimen is based on each institutional practice.

### Patient assessment

#### Basic characteristic data of patient

After patient signs informed consent form, the basic data including age, ECOG performance status, type of cancer and staging, plan of radiotherapy and chemotherapy will be collected.

#### Side effect evaluation

Radiotherapy acute side effect will be evaluated by CTCEA version 5 in weekly basis during radiotherapy in the following items.

- Oral mucositis
- Radiation dermatitis
- Esophagitis
- Laryngeal mucositis
- Pharyngeal mucositis
- Hematologic
  - Anemia
  - Decreased White blood cell
  - Decreased Neutrophil count
  - Decreased Lymphocyte count
  - Decreased Platelet count

Patients will also evaluate the oral mucositis and radiation dermatitis toxicities by themselves using Thai version of NCI- PRO-CTCAE.

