#### Nutritional status

All patients will receive nutrition consultation every visit.

| Items            | Screening | 1-2 week before RT | Week during radiotherapy |   |   |   |   |   |   |
|------------------|-----------|--------------------|--------------------------|---|---|---|---|---|---|
|                  |           |                    | 1                        | 2 | 3 | 4 | 5 | 6 | 7 |
| Informed consent | x         |                    |                          |   |   |   |   |   |   |
| Demographic data | x         |                    |                          |   |   |   |   |   |   |
| Randomization    | x         |                    |                          |   |   |   |   |   |   |
| CBC              |           | x                  | x                        | x | x | x | x | x | x |
| BUN/Cr           |           | x                  | x                        | x | x | x | x | x | x |
| Albumin          |           | x                  | x                        |   |   | x |   |   | x |

|        |  |   |   |   |   |   |   |   |   |
|--------|--|---|---|---|---|---|---|---|---|
| CTCEA  |  | x | x | x | x | x | x | x | x |
| Weight |  | x | x | x | x | x | x | x | x |
| Height |  | x | x | x | x | x | x | x | x |

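### No nausea, vomiting or diarrhea grade is scheduled in either arm, so gastrointestinal tolerability of the supplement will have no control-arm comparator

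*Protocol*

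**What the plan says.** - **Clinician grading.** Protocol, Side effect evaluation: "Radiotherapy acute side effect will be evaluated by CTCEA version 5", weekly during radiotherapy, for a stated set of items. These are oral mucositis, radiation dermatitis, esophagitis, laryngeal mucositis, pharyngeal mucositis, anemia, and decreased white cells, neutrophils, lymphocytes and platelets.
- **Patient report.** Same section: "Patients will also evaluate the oral mucositis and radiation dermatitis toxicities by themselves", using the Thai PRO-CTCAE. No other symptom is named.
- **Schedule.** The table under Nutritional status has one toxicity-grading row, marked at the "1-2 week before RT" column and at weeks 1 to 7. It has no separate adverse-event row.
- **Exposure.** Nutrition support: "Participant who is randomized into IN arm will receive IN 1 week before radiotherapy and daily during radiotherapy". The dose is three sachets a day, 762.48 kcal. The control arm receives no supplement.
- **Ungraded information.** Same section: "Both arms will receive nutrition consultation every visit to ensure adequate energy intake", and the consultation also covers side effects. Patients with "symptoms that limit intake such as nausea, vomiting, dysphagia, or odynophagia" are evaluated and treated by their physician. On sachets: "The remaining IN package will be counted in every visit".
- **Stopping rule.** Same section, in part: "including grade III-IV toxicity caused by IN, the IN will be withdrawn". The Discontinuation section repeats the rule for the study product.
- **Shared background treatment.** Chemotherapy: weekly cisplatin or carboplatin during radiotherapy in both arms, with induction chemotherapy allowed.

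**The concern.** The protocol treats nausea and vomiting as expected barriers to taking the supplement, and it makes graded product toxicity a reason to stop it. It then leaves both symptoms off the list of what is graded. Weekly platinum can cause the same symptoms in every patient. A count of nausea or vomiting among IN patients means little unless the same count, made in the same way, exists among controls.

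At stake is the answer to a practical question: how well do patients tolerate a large daily oral supplement during chemoradiotherapy? Secondary objective 2, on comparing other acute side effects between arms, would also be served less fully than it could be. Such a gap cannot be left to a statistical analysis plan, which can only analyze what has been recorded.

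**Working it through.** **1. Coverage.** Clinician-graded items: 5 mucosal or skin + 5 hematologic = 10, of which 0 are nausea, vomiting or diarrhea. Patient-reported toxicities: 2, of which 0 are. Esophagitis is on the list, but as a radiotherapy effect; it does not measure nausea, vomiting or diarrhea.

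**2. Could another source give a graded rate by arm?**
- Nutrition consultation: both arms, but no grade is stated.
- Physician evaluation of symptoms: when they occur, with no grade and no scheduled record.
- Sachet count: IN arm only, and it does not say why sachets were left.
- Stopping rule: implies a grade, but toxicity caused by IN can arise only in the IN arm.
- Weekly weight and BUN/creatinine: both arms, but these are consequences rather than symptom grades, and weight also reflects the added calories.

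None gives a graded control-arm rate.

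**3. The planned sample size, used below.** Inputs from the Sample size section: 61% against 30.5%, power 0.80, and 0.05 (labelled beta there, read here as two-sided alpha). With pooled variance, p̄ = 0.4575:

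n = [1.96·√(2 × 0.4575 × 0.5425) + 0.8416·√(0.61 × 0.39 + 0.305 × 0.695)]² / 0.305² = 40.7, so 41 per arm.

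41 / 0.85 = 48.2, so 49. Both figures reproduce. The protocol rounds to 50 per arm; after 15% dropout, 50 × 0.85 = 42.5, or about 42.

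**4. Precision if the symptoms were graded.** The protocol gives no rates for these symptoms, so all rates here are assumptions. Half-width of the 95% interval for a difference = 1.96·√[(p₁(1−p₁) + p₂(1−p₂))/n].

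| Control vs IN | Half-width, n = 50 | Half-width, n = 42 | Power, n = 50 | Power, n = 42 |
|---|---|---|---|---|
| 10% vs 20% | 13.9 points | 15.1 | 0.29 | 0.25 |
| 20% vs 30% | 16.9 | 18.4 | 0.21 | 0.18 |
| 30% vs 40% | 18.6 | 20.3 | 0.18 | 0.16 |

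For the first cell: 1.96·√[(0.09 + 0.16)/50] = 1.96 × 0.0707 = 0.139. Power is two-sided at 0.05, pooled-variance normal approximation. For 80% power against a 10% control rate, the IN rate would have to reach about 32.7% at 50 per arm, or 35.3% at 42.

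**5. What the missing comparator hides.** Suppose 30% of IN patients had grade 2 or higher nausea. With the control rate unknown between 10% and 40%, the difference could lie anywhere from +20 to −10 points. With controls graded at 50 per arm, a 10% control rate would give +20 points (95% CI +5 to +35), and a 30% rate would give 0 (−18 to +18).

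**6. Burden.** The toxicity row has 1 + 7 = 8 assessments. Two items: 2 × 8 = 16 grades per patient, 1,600 for 100 patients. Three items: 24 per patient, 2,400 in all.

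**The case against.** The best defense is that this was a choice about scope. The list is headed as acute effects of radiotherapy, it is consistent with secondary outcome 1, and no objective or endpoint promises a gastrointestinal tolerability comparison. The case report form is not shown, and the stopping rule suggests some grading beyond the list. The Literature Review also reports that the investigators' earlier randomized trial of IN found no difference in non-hematologic toxicities.

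Part of this stands. A reader might infer that the protocol contradicts its own secondary outcome; it does not, because that outcome can be met with the listed items. A reader might also infer that these symptoms go unattended; they do not, because consultation and physician evaluation are provided.

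The rest does not close the gap. Grading implied by the stopping rule concerns one arm only. The earlier result is not itemized by symptom in the protocol, and the dose now is about 1.5 times higher (arginine 9.39 / 6.16 = 1.52).

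A second objection is that grading would settle little. That is right for moderate effects: power for a 10-point excess is 18% to 29% at 50 per arm, and the trial is open-label. It limits what the data could show, but it does not justify having no comparator.

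**Conclusion.** The gap is real and modest. No nausea, vomiting or diarrhea grade is scheduled in either arm, so the trial will have no control-arm comparator for gastrointestinal tolerability of IN. The primary endpoint, sample size and randomization are untouched. The finding rests on reading the item list as what will be graded; the protocol schedules nothing further.

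Three stronger readings should be resisted:

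- **That control-arm grades would attribute symptoms to IN or clear it of them.** At 50 per arm and without blinding, only a large excess could be shown, for example from 10% to about 33%.
- **That the week of IN before radiotherapy gives a clean view of the supplement.** It comes before the weekly platinum, but induction chemotherapy is allowed and its effects may persist.
- **That diarrhea has the same standing as nausea and vomiting.** The protocol mentions it only in the background review, so the case for it is weaker.

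This is a cheap improvement worth making, not a threat to the trial's main conclusion.

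**What to change.** - **Items.** Add nausea and vomiting to the CTCAE v5 form in both arms, at the existing pre-radiotherapy and weekly assessments. Diarrhea is an optional third item.
- **Baseline.** Use the pre-radiotherapy grade: before the first sachet in the IN arm, and at the same pre-radiotherapy visit in the control arm.
- **Week 1.** Have this grade cover the whole period since the baseline visit, so that the first week of IN is included.
- **Reporting.** Give worst grade by arm, with the difference and its 95% confidence interval, as a descriptive tolerability outcome separate from secondary outcome 1.

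The cost is two or three lines on a form already completed at eight assessments, plus the baseline and week 1 instructions. No visit, test or patient is added. Weekly grading takes slightly longer, and the resulting data will be open-label and imprecise.
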